## Abstract

**Background:**

Postoperative insomnia is one of the common complaints caused by spinal metastatic cancer surgery. It affects patients’ functional recovery, greatly reduces their quality of life, and adversely impacts disease prognosis. Compared with traditional pharmacological treatments, acupuncture is an alternative therapy for postoperative insomnia. However, standardized, high-quality randomized controlled trials on electroacupuncture for postoperative insomnia in patients with spinal metastasis (SM) are scarce, and there is a lack of clear inclusion criteria for this specific population. Postoperative insomnia in patients with SM has distinct clinical characteristics compared with general cancer-related insomnia, necessitating targeted investigation.

**Objective:**

This study aims to evaluate the efficacy and safety of electroacupuncture in the treatment of postoperative insomnia in patients with SM, and to provide high-level clinical evidence for the inclusion of electroacupuncture in the clinical management plan of postoperative insomnia in patients with SM.

**Methods:**

This is a study protocol for a randomized controlled trial. We will randomly assign 196 patients with insomnia after spinal metastatic cancer surgery to the acupuncture group (n=98) or the control group (sham acupuncture group; n=98). All participants will be treated on the first day after surgery and receive 12 sessions in total (30 min per session, 3 sessions per wk for 4 weeks). The primary outcome is the change in Pittsburgh Sleep Quality Index score from baseline to post treatment (wk 4). The secondary outcomes include actigraphy records (sleep efficiency, number of sleep awakenings, total sleep time, sleep latency, and wake after sleep onset), Insomnia Severity Index, Spine Oncology Study Group Outcomes Questionnaire 2.0, and Patient Health Questionnaire-9. All results will adhere to the intention-to-treat principle and will be evaluated at baseline, posttreatment (wk 4), and follow-up (wk 12).

**Results:**

This study was funded in June 2023 (supported by the Project of Shanghai Municipal Health Commission, National Natural Science Foundation of China, etc). Recruitment will start in mid-2026 and end in December 2027. Data collection will be completed in October 2027, and data analysis is expected to be finished in December 2027. The results of this study are anticipated to be published in the first half of 2028.

**Conclusions:**

This study is designed to rigorously assess the therapeutic value of electroacupuncture for postoperative insomnia in patients with SM. If proven effective, electroacupuncture is expected to become a safe and feasible alternative or complementary therapy for this population, reducing reliance on hypnotic drugs and improving patients’ quality of life and prognosis. The results will fill the gap in current clinical evidence for electroacupuncture in the treatment of spinal metastatic postoperative insomnia and provide a basis for the optimization of clinical treatment strategies.

## Introduction

Spinal metastasis (SM) is a common complication in the advanced stages of malignant tumors, with reported prevalence ranging from approximately 40% to 70% among patients with systemic cancer. SM frequently leads to vertebral destruction, spinal instability, and neural element compression, resulting in pain, neurological dysfunction, impaired motor function, and, in severe cases, paralysis [1-4].

As many as 26% of patients with cancer suffer from insomnia, and postoperative rehabilitation and care for these patients is a heavy social burden. Insomnia is a common consequence after SM surgery, mainly manifesting as difficulty falling asleep, easy awakening, insufficient sleep time, and poor sleep quality. Patients often feel fatigued after waking [5,6]. Studies have shown that insomnia not only affects patients’ functional recovery, daily living ability, quality of life, physical and mental health, and neurological rehabilitation but also impacts cancer prognosis. It can lead to decreased immune function in patients with cancer, increased expression of cancer-promoting factors, and higher mortality [7,8]. In addition, survivors of cancer with persistent insomnia frequently present with comorbid anxiety and depressive symptoms, which, if left untreated, may further compromise immune function, reduce survival, and substantially diminish overall quality of life [9,10].

Numerous randomized controlled trials (RCTs) have evaluated the efficacy and safety of electroacupuncture for cancer-related insomnia (CRI), but SM postoperative insomnia has unique characteristics that distinguish it from general CRI. First, the pathogenesis is more complex; SM surgery involves spinal structure reconstruction, which may cause persistent postoperative pain, limited spinal movement, and neurological irritation, all of which directly interfere with sleep initiation and maintenance. In contrast, general CRI is more often associated with systemic symptoms such as tumor-related fatigue, anxiety, and drug side effects. Second, the sleep disturbance pattern is specific; patients with postoperative SM often experience sleep fragmentation due to nocturnal pain and positional restrictions, while general CRI is more likely to present as difficulty falling asleep or early awakening. Third, the rehabilitation context differs; patients with SM are in a critical period of spinal function recovery, and sleep quality directly affects tissue repair and neurological function restoration, whereas general CRI has a more indirect impact on disease progression. These unique characteristics indicate that the efficacy and mechanism of electroacupuncture for SM postoperative insomnia may differ from those for general CRI, justifying the necessity of this targeted study.

Studies in recent years have further confirmed the multifaceted adverse impact of postoperative insomnia on patients with SM. In terms of physical recovery, insomnia can reduce the body’s immune function, inhibit the repair of damaged tissues, and delay the recovery of postoperative motor and neurological functions [11-13]. In terms of disease prognosis, insomnia can up-regulate the expression of cancer-promoting factors (such as IL-6 and TNF-α), increase the risk of tumor recurrence and metastasis, and reduce the overall survival rate of patients [14-16]. In terms of mental health, long-term insomnia is closely associated with anxiety, depression, and other negative emotions, which further aggravates the decline in quality of life [17,18]. A 2023 study by Kim et al [8] found that CRI can mediate the impact of sleep disturbance on disease progression fear in patients with postoperative lung cancer, highlighting the importance of intervening in insomnia.

At present, the clinical treatment of postoperative insomnia mainly relies on pharmacological methods. Commonly used drugs include benzodiazepines, new nonbenzodiazepines, and antidepressants [19]. Although these drugs can temporarily improve sleep symptoms, long-term use is prone to tolerance, addiction, cognitive impairment, and other adverse reactions [20,21], making them unsuitable for patients with SM who need long-term rehabilitation. Therefore, exploring safe and effective nonpharmacological therapies has become an urgent clinical need.

As a nonpharmacological treatment of Traditional Chinese Medicine, acupuncture exerts therapeutic effects on insomnia by inserting needles at specific body points. A study found that acupuncture is effective and safe in treating insomnia, worthy of clinical promotion, and may be a promising nonpharmacological alternative therapy [22]. Due to its efficacy and safety, electroacupuncture is being used to treat insomnia and relieve cancer-related symptoms [23]. Electroacupuncture, as an important part of Traditional Chinese Medicine, acts on specific acupoints of the human body through acupuncture needles and electrical stimulation, regulating the body’s functional state to soothe the nerves and improve sleep. A meta-analysis by Zhao et al [22] confirmed that acupuncture is effective and safe for primary insomnia, significantly improving patients’ sleep quality [24]. Another systematic review by Guo et al [25] pointed out that acupuncture-related therapies have potential advantages in the treatment of CRI, but the quality of evidence is limited. However, most existing studies focus on general CRI, lacking targeted research on SM postoperative insomnia. Patients with SM have unique clinical characteristics such as postoperative pain, spinal instability, and neurological damage, which may affect the efficacy of electroacupuncture. In addition, existing studies have problems, such as small sample sizes, single-center designs, and unclear inclusion criteria, resulting in insufficient reliability and generalizability of results.

This study aims to fill the gap in existing research by conducting a prospective, multicenter, RCT. The specific research hypotheses are (1) electroacupuncture can significantly improve the sleep quality of patients with postoperative insomnia after SM, as reflected by the reduction of Pittsburgh Sleep Quality Index (PSQI) score; (2) electroacupuncture can improve sleep-related objective indicators (sleep efficiency, total sleep time [TST], etc), reduce the severity of insomnia, improve quality of life, and alleviate depressive symptoms; (3) electroacupuncture is safe for patients with postoperative SM, with a low incidence of adverse events (AEs). Through this study, we expect to provide high-level clinical evidence for the application of electroacupuncture in the treatment of SM postoperative insomnia and offer a new treatment option for clinical practice.

## Methods

### Study Design and Setting

This will be a 16-week prospective, multicenter RCT carried out at 4 clinical institutions, including (1) Longhua Hospital, Shanghai University of Traditional Chinese Medicine; (2) Shanghai Municipal Hospital of Traditional Chinese Medicine, Shanghai University of Traditional Chinese Medicine; (3) Hangzhou TCM Hospital, Zhejiang Chinese Medical University; (4) Shanghai Tonghe Orthopedic Hospital; and (5) Department of Spine, Yueyang Hospital of Integrated Traditional Chinese and Western Medicine, Shanghai University of Traditional Chinese Medicine, Shanghai (200437), China.

The 16-week study period (4-wk treatment+8 wk follow-up) is determined based on the characteristics of postoperative recovery and the therapeutic cycle of electroacupuncture. The postoperative recovery of patients with SM is a long process, and sleep disturbance may persist for several months. A 4-week treatment cycle is consistent with the conventional course of acupuncture for insomnia, facilitating the observation of immediate therapeutic effects [26]. The 8-week follow-up period can further evaluate the sustainability of the therapeutic effect and whether insomnia symptoms rebound, which is of great significance for guiding long-term clinical management. Previous studies have shown that the therapeutic effect of electroacupuncture on insomnia can be maintained for 1‐3 months after treatment, so an 8-week follow-up is set to fully observe the long-term effect [27,28].

The schedule of treatment assessments and data collection is presented in Table 1. The trial protocol was developed in accordance with the SPIRIT (Standard Protocol Items: Recommendations for Interventional Trials) 2013 guidelines, and the Standards for Reporting Interventions in Clinical Trials of Acupuncture (STRICTA) to ensure methodological rigor and transparency of the intervention reporting [29,30]. There is a deviation in recruitment timeline. The initial recruitment start date recorded in the trial registry was May 2025. Owing to logistical preparation and multicenter institutional coordination for the study, the recruitment timeline has been revised and the confirmed start date is March 2026, which is the actual operational schedule for this trial.

**Table 1. T1:** Schedule of enrollment, interventions, and assessments.

Study period	Time point (wk)							
	Enrollment		Intervention				Follow-up period	
	Week –1	Week 0	Week 1	Week 2	Week 3	Week 4	Week 8	Week 16
Eligibility screening	✓							
Informed consent	✓							
Medical history	✓							
Randomization		✓						
Intervention								
Electroacupuncture			✓	✓	✓	✓		
Sham electroacupuncture			✓	✓	✓	✓		
Primary outcomes								
PSQI^a^		✓				✓	✓	✓
Secondary outcomes								
Actigraphy		✓				✓	✓	✓
ISI^b^		✓				✓	✓	✓
SOSGOQ 2.0^c^		✓				✓	✓	✓
PHQ-9^d^		✓				✓	✓	✓
Other assessment								
Safety of electroacupuncture			✓	✓	✓	✓		
Adverse events			✓	✓	✓	✓	✓	✓
Assessment of credibility		✓						
Assessment of blinding success						✓		

a PSQI: Pittsburgh Sleep Quality Index.

b ISI: Insomnia Severity Index.

c SOSGOQ 2.0: Spine Oncology Study Group Outcomes Questionnaire 2.0.

d PHQ-9: Patient Health Questionnaire-9.

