### Patients and Participants

#### Overview

We will inform the participants of the study protocol and obtain written informed consent before screening them according to the eligibility criteria. The included participants will be randomly allocated at 1:1 to receive 4-week electroacupuncture treatment (electroacupuncture group) or sham electroacupuncture treatment (sham electroacupuncture group). We will then conduct an 8-week follow-up for further observation. All procedures will rigorously adhere to the Declaration of Helsinki. The inclusion and exclusion criteria are described below.

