##### Secondary Outcome Analysis

Actigraphy indicators (SOL, TST, sleep efficiency, WASO, and number of sleep awakenings): Between-group comparisons of changes from baseline to posttreatment (wk 4) and follow-up (wk 12) will be performed using ANCOVA, with corresponding baseline values and the same covariates as the primary outcome.

ISI, SOSGOQ 2.0, and PHQ-9 scores: Similar to the primary outcome, ANCOVA will be used to compare the between-group differences in score changes at each time point. If the data do not meet the normality assumption, nonparametric tests (Mann-Whitney *U* test for between-group comparisons and Wilcoxon signed-rank test for within-group comparisons) will be used as alternatives.

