## Results

This study is a prospective RCT that has completed the study design and obtained ethical approval. This study was funded in June 2023. It was supported by the Project of Shanghai Key Discipline Construction Project of Traditional Chinese Medicine (Clinical Category): Digital Intelligence Acupuncture (shzyyzdxk-2024108); the Project of Shanghai Municipal Health Commission (20204Y0165, 20224Y0165); the National Natural Science Foundation of China (82205145); Shanghai “Rising Stars of Medical Talents”-Youth Development Program-Youth Medical Talents-Specialist Program (SHWSRS 2023‐062); the Youth Talent Lifting Project of the Chinese Society of Traditional Chinese Medicine (2023-QNRC2-A03); and the “Visit Famous Schools and Worship Famous Teachers” Project of Shanghai University of Traditional Chinese Medicine (079). The funders had no role in the design of the study, data collection, analysis, interpretation of data, or writing of the manuscript.

Participant recruitment is projected to start in mid-2026 and end in December 2027, with a planned recruitment of 196 participants from 5 clinical institutions. As of the submission of this manuscript, the research team has completed the training of researchers, the preparation of study materials (such as informed consent forms, CRFs, and scales), and the debugging of equipment (electroacupuncture devices and actigraphy devices). The baseline characteristics of participants will be collected after recruitment starts, including age, sex, tumor type, surgical method, time since surgery, PSQI score, ISI score, etc

Data collection will be completed in October 2027, including baseline assessment (wk 0), treatment process records (weekly), posttreatment assessment (wk 4), and follow-up assessment (wk 12). Actigraphy monitoring will be conducted at week 0, week 1, week 2, week 3, and week 4 to collect objective sleep data. AEs will be recorded in real-time during the study period.

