### Limitations

Despite the rigorous design, this study still has some limitations. First, blinding limitations: although Streitberger placebo needles are used for the sham electroacupuncture group, acupuncturists are aware of the grouping, which may lead to performance bias. However, we have taken measures, such as separate treatment rooms and eye masks for patients to minimize this bias. Second, follow-up period: the follow-up period of this study is 8 weeks, which may not be sufficient to evaluate the long-term efficacy of electroacupuncture. Future studies can extend the follow-up period to observe the sustainability of the therapeutic effect. Third, lack of mechanism exploration: this study focuses on clinical efficacy and safety, and does not explore the underlying mechanism of electroacupuncture in improving sleep. Future studies can combine biological indicators (such as neurotransmitters and cytokines) to explore the mechanism. Fourth, exclusion criteria limitations: the study excludes patients with severe comorbidities, mental disorders, and chronic insomnia disorder, which may limit the generalizability of the results to the entire population with postoperative SM. Fifth, potential confounding factors: although we have adjusted for common confounding factors in the statistical analysis, there may still be unmeasured confounding factors (such as postoperative pain intensity and family support) that affect the study results. Finally, single-blind design: due to the characteristics of acupuncture treatment, it is difficult to implement double-blinding (acupuncturists cannot be blinded). This may introduce potential bias, but single-blinding of patients and outcome assessors can still reduce the impact of subjective factors.

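### The follow-up calendar contradicts itself (week 12 against weeks 8 and 16), so the time point for the secondary durability comparisons, above all actigraphy, is not fixed

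*Protocol article*

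**What the plan says.** Study Design and Setting gives the overall length: "The 16-week study period (4-wk treatment+8 wk follow-up) is determined based on the characteristics of postoperative recovery". Two other sections repeat the eight weeks. Patients and Participants (Overview) says "We will then conduct an 8-week follow-up for further observation", and Limitations says "the follow-up period of this study is 8 weeks".

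The same Study Design section refers the reader to Table 1, titled "Schedule of enrollment, interventions, and assessments". Its two follow-up columns are week 8 and week 16. PSQI, actigraphy, ISI, SOSGOQ 2.0 and PHQ-9 are all ticked at weeks 0, 4, 8 and 16.

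The Abstract (Methods) instead says that all results "will be evaluated at baseline, posttreatment (wk 4), and follow-up (wk 12"). The Results section also lists a week-12 follow-up assessment.

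For actigraphy, Secondary Outcome Analysis says: "Between-group comparisons of changes from baseline to posttreatment (wk 4) and follow-up (wk 12) will be performed using ANCOVA". Results says: "Actigraphy monitoring will be conducted at week 0, week 1, week 2, week 3, and week 4 to collect objective sleep data". The Intervention section gives the same weeks 0 to 4 list. For ISI, SOSGOQ 2.0 and PHQ-9 the analysis names no week: "ANCOVA will be used to compare the between-group differences in score changes at each time point".

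**The concern.** The stated reason for the follow-up is to learn whether the effect lasts or the insomnia returns. That requires one agreed time at which outcomes are measured and compared. The article gives sites a visit table with one set of follow-up weeks and gives analysts a different week.

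A mismatch of this kind does not correct itself. A participant who passes week 12 without a visit cannot be measured at week 12 later. If data then exist at weeks 8 and 16, someone has to decide which of them stands in for week 12, or whether both do, after collection has begun. For actigraphy, the trial's only objective sleep measure, one of the stated schedules lists no recording after treatment at all.

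**Working it through.** **1. The study length.** Inputs from Study Design and Setting: 4 weeks of treatment, 8 weeks of follow-up, stated total 16 weeks.

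- Sum of the parts: 4 + 8 = 12. The stated 16 is not reproduced.
- Adding the week -1 screening period: 12 + 1 = 13. Still not 16.
- Follow-up needed for a last visit at week 16: 16 - 4 = 12 weeks, against the 8 weeks stated in three sections.

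**2. Could Table 1 count its follow-up weeks from the end of treatment?** Week 8 would become study week 8 + 4 = 12, which fits. Week 16 would become study week 16 + 4 = 20, which fits neither 12 nor 16. This reading does not rescue the table.

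**3. The places side by side.**

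| Place in the article | Times given |
|---|---|
| Abstract, Methods | all outcomes at baseline, 4, 12 |
| Study Design and Setting | total 16; treatment 4 + follow-up 8 |
| Table 1 | all five instruments at 0, 4, 8, 16 |
| Patients and Participants, Overview | follow-up 8 weeks after 4 of treatment, so 12 |
| Intervention | actigraphy at 0, 1, 2, 3, 4 |
| Secondary Outcome Analysis | actigraphy change to 4 and to 12; questionnaires at each time point |
| Results | assessments at 0, 4, 12; actigraphy at 0, 1, 2, 3, 4 |
| Limitations | follow-up 8 weeks |

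**4. Actigraphy: analysis weeks against collection weeks.** The post-baseline analysis weeks are {4, 12}.

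- Against Table 1 {0, 4, 8, 16}: only week 4 is covered.
- Against the Intervention and Results lists {0, 1, 2, 3, 4}: only week 4 is covered.
- Against the Abstract's general statement {0, 4, 12}: both are covered.

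Neither schedule that names actigraphy week by week contains week 12. The analyses affected are the five actigraphy variables (sleep latency, total sleep time, sleep efficiency, wake after sleep onset, number of awakenings) at follow-up.

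**5. The questionnaires.** Comparison at each time point can be carried out on either calendar. What differs is the set of times: {4, 12} on one, {4, 8, 16} on the other.

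**6. What a late choice could cost (illustration only).** Suppose the more favourable of two follow-up weeks is reported for one outcome, each tested at 0.05. The chance of a false positive runs from 5% if the two tests are fully correlated to 1 - 0.95² = 9.75% if they are independent. The true correlation is not given in the article.

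**7. The primary endpoint.** PSQI change to week 4 is collected at week 4 in Table 1, in the Abstract and in Results, and is analysed at week 4. No conflict arises.

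**The case against.** A reader might infer that the durability comparison will have no data. The article does not support that. The Abstract and Results both plan a week-12 assessment, and the Abstract's statement covers actigraphy. Table 1, if followed, gives post-treatment data at weeks 8 and 16. On either calendar there are follow-up data; what is missing is agreement on when. The absence of data is conditional: none at week 12 under Table 1, and no actigraphy after week 4 under the Intervention and Results lists.

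Those lists may describe monitoring during treatment and do not expressly exclude later wear. That is fair, and it means they do not prove that the follow-up actigraphy comparisons cannot be made. It does not reconcile them with Table 1, which omits weeks 1 to 3, or with an analysis at week 12.

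A reader might also count PSQI durability and all the questionnaires as lost. That goes too far. The primary analysis section specifies no PSQI ANCOVA after week 4, and the questionnaire analysis is not tied to a named week.

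Finally, the article promises a signed statistical analysis plan before data lock and unblinding, and blinds the statisticians. This limits a choice driven by results, and the article openly leaves secondary outcomes unadjusted with cautious interpretation. These safeguards stand. However, a plan signed before data lock can come after the visits, and it cannot create measurements at a week when nobody was seen. Nor is this detail left to a fuller document: the article states the visit times, and states them incompatibly.

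**Conclusion.** The point holds as an internal contradiction. The 16-week label does not equal its own parts (12). Follow-up falls at week 12 in the Abstract, the actigraphy analysis and Results, but at weeks 8 and 16 in Table 1. Actigraphy has two explicit collection schedules, neither of which contains the follow-up week named for its analysis.

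The consequence is that the time point for the secondary durability comparisons is not fixed. It is sharpest for the five actigraphy variables, where following Table 1 leaves the week-12 ANCOVA without observed data. The primary endpoint at week 4 is untouched, and so is the trial's main conclusion.

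This rests on Table 1 being the schedule sites would use, as Study Design and Setting implies, and on its columns having been read intact. The 16-week wording in the text agrees with the week-16 column, which supports that reading. The article does not settle which calendar was intended.

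**What to change.** Before recruitment, choose one calendar and write it identically in the Abstract, Study Design and Setting, Table 1, Patients and Participants (Overview), Intervention, Secondary Outcome Analysis, Results and Limitations. Two routes are consistent:

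- Replace the week 8 and week 16 columns of Table 1 by week 12, and call the study 12 weeks long.
- Keep weeks 8 and 16, restate the follow-up as 12 weeks wherever 8 is given, change the ANCOVA time points to match, and name one of the two as the main follow-up.

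On either route, schedule actigraphy at every time point at which it is analysed, or delete the analysis time points at which it is not worn. State whether the weeks 1 to 3 recordings are also intended, and show them in Table 1 if so.

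The cost is mainly wording. Against the weeks 0 to 4 list, a week-12 calendar adds one actigraphy wearing period and a weeks 8 and 16 calendar adds two. Against Table 1 as it stands, the first route replaces two follow-up visits by one at a new week, and the second changes no visits.

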### Randomization and Allocation Concealment

The random allocation scheme for this trial will be generated by The Clinical Research Center of Shanghai Municipal Hospital of Traditional Chinese Medicine, Shanghai University of Traditional Chinese Medicine. We will use stratified block randomization with centers as a stratification factor for group inclusion. When blocks are used up, centers will inform the data management center for replenishment. Independent investigators will place the treatment assignment code in consecutively numbered opaque envelopes based on the order of patients’ visits. All participants will be informed that they have the same probability of being assigned to the electroacupuncture group or the sham electroacupuncture group. Participants and researchers will not know the grouping in advance. To ensure the reliability of the research, all researchers will strictly abide by the principle of departmental separation and receive standardized training before implementation.

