### Assessments and Outcomes Measurement

#### Primary Outcome

The PSQI will be the primary outcome of this trial. The cross-cultural adaptation of PSQI into simplified Chinese was successful, with good reliability and validity for comprehensively evaluating the sleep quality of patients with insomnia [31]. Furthermore, PSQI is widely used to assess the effect of cancer treatment on sleep quality in patients with cancer. PSQI comprises 19 self-assessment items and is composed of 7 subscales, including sleep quality, falling asleep time, sleep duration, sleep efficiency, sleep disorders, hypnotic drug use, and daytime dysfunction. Each component is scored on a scale of 0‐3, and the total scores of PSQI range from 0 to 21. The higher the patients’ score, the worse their sleep quality and the more severe the sleep disorders, and vice versa. The primary outcome is defined as the change in PSQI total score from baseline (wk 0) to posttreatment (wk 4).

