### Assessment of Credibility

The Credibility Assessment Questionnaire is applied to assess the reliability and credibility of the trial, including the selection of the control group, the implementation of the blinding method, and the details of electroacupuncture treatment. The Credibility Assessment Questionnaire is used in electroacupuncture trials to improve the accuracy and repeatability of the trials. We will ask participants in this trial to rate the following questions on a 6-point scale: (1) How confident are you that this treatment can alleviate your complaints?; (2) If your friends also have similar complaints, how confident would you be in recommending this treatment method to them?; (3) How logical do you think this treatment is?; and (4) How successful do you think this treatment is in reducing other complaints? [45].

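### The only credibility rating is taken at Week 0, before any session, so it measures baseline expectancy and cannot show whether the sham was as credible as real electroacupuncture

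*Protocol article*

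**What the plan says.** Table 1, under Study Design and Setting, has the time columns "Week –1 Week 0 Week 1 Week 2 Week 3 Week 4 Week 8 Week 16". The row "Assessment of credibility" has one tick, at Week 0, the column that also holds randomization and the baseline scales. The row "Sham electroacupuncture" and the row for real electroacupuncture are both ticked at Weeks 1, 2, 3 and 4 and nowhere else. A separate row for blinding success has one tick, at Week 4.

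The Assessment of Credibility section describes four items rated by participants on a 6-point scale. It sets the questionnaire a broad aim, namely to show how far the study can be trusted, "including the selection of the control group, the implementation of the blinding method, and the details of electroacupuncture treatment". The items refer to the treatment as something the participant can judge; the fourth asks "How successful do you think this treatment is in reducing other complaints". The section names no time point, and no other section adds a later administration.

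On what participants know beforehand, Randomization and Allocation Concealment states: "All participants will be informed that they have the same probability of being assigned to the electroacupuncture group or the sham electroacupuncture group". It adds that the grouping is not known in advance.

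**The concern.** A credibility questionnaire in a sham-controlled trial is normally there to show that participants found the sham as believable as the real procedure. That can be judged only after they have experienced one or the other. Here the one scheduled rating comes before anyone has felt a needle, a placebo needle or the device.

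The question is a live one in this design. The real arm receives skin penetration, manipulation to produce Deqi, and a 2 to 5 mA current. The sham arm receives a blunt needle that does not penetrate, with the device connected but delivering nothing. Participants wear eye patches during treatment, so bodily sensation is likely to be a main cue to allocation. The acupuncturist knows the allocation, and the Limitations section accepts that this may lead to performance bias. The primary outcome is self-reported. The Discussion's section on the sham method asserts that the chosen sham secures blinding. A comparison of credibility between arms after exposure would help test that assertion; the scheduled one does not.

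**Working it through.** The plan gives no figure on this point, so the check sets the schedule against the stated purpose.

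**1. Order of events from Table 1**

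| Item | Ticked at |
|---|---|
| Randomization | Week 0 |
| Credibility rating | Week 0 only |
| Real electroacupuncture | Weeks 1, 2, 3, 4 |
| Sham electroacupuncture | Weeks 1, 2, 3, 4 |
| Blinding success | Week 4 only |

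The Primary Outcome section also treats week 0 as baseline. The credibility rating therefore precedes every session.

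**2. What a Week 0 comparison can detect**

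Let C0 be the Week 0 rating and C1 a rating after an early session. The quantity that bears on the sham is

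d1 = E[C1 | real] − E[C1 | sham].

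The quantity available is

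d0 = E[C0 | real] − E[C0 | sham].

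Allocation is random, participants do not know it, both arms have had the same information, and neither has had a session. Hence d0 = 0 whatever the value of d1. A two-sided test of C0 between arms at the protocol's α = .05 rejects about 5% of the time whether the sham is fully convincing or not convincing at all. As a test of the sham as experienced, it has no power beyond its error rate.

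**3. Purpose against timing**

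The stated purpose includes the choice of control, how blinding was carried out and the details of treatment. At Week 0 participants have met none of these. They can answer the four items only from prior expectation. That is a legitimate measurement, but not the one described.

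**4. What the Week 4 assessment adds**

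Treatment is 3 sessions a week for 4 weeks, so by Week 4 a participant has had up to 3 × 4 = 12 sessions. A guess at allocation then can reflect how convincing the procedure felt, how much sleep has improved, or both. If real treatment works, guesses can differ between arms even with a good sham. The assessment is informative, but it does not separate the two explanations cleanly.

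**The case against.** The strongest reply is that the trial does not depend on this questionnaire. Blinding success is assessed at Week 4. Participants wear eye patches and are treated in different rooms, outcome assessors are blinded, both arms use the same acupoints, and the placebo needle is designed to imitate insertion. Actigraphy supplies objective secondary outcomes. All of this stands. A reader might infer that the trial has no check of the sham, or that a positive PSQI result could not be distinguished from unequal credibility at all. The documents support neither reading. The Week 4 check is weakened by possible confounding with perceived benefit, not removed, and the actigraphy results would bear on interpretation.

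A reader might also infer that the Week 0 rating is worthless. That goes too far. The item on confidence that the treatment will help looks forward and can be answered before treatment. The score describes baseline expectancy and its balance between arms, and could serve as a covariate. The order of events within Week 0 is not given, and the Intervention section has an unblinded acupuncturist conducting allocation. If the rating follows randomization, a difference between arms could point to leaked allocation. The zero expected difference holds only while allocation stays hidden.

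Two further replies have some weight. The purpose sentence is broad, and four participant ratings could not assess everything it lists at any visit, so part of the mismatch lies in the wording. Table 1 also disagrees with the text elsewhere: its last visit is Week 16, where the analysis text has week 12, and its actigraphy ticks differ from the weekly recording described under Intervention. The single credibility tick could be a table error. But no passage gives another time, so the mismatch needs correcting either way.

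Finally, no planned analysis in the article uses the credibility score, so moving it alters no estimate or error rate. That is correct and limits the seriousness of the point.

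**Conclusion.** The point holds in a limited form. The only scheduled credibility rating precedes all real and sham sessions. It measures baseline expectancy and cannot show whether the non-penetrating, no-current sham was as credible as real electroacupuncture, which does not fit the purpose the article gives it. For that question the Week 0 comparison has an expected difference of zero. This rests on two assumptions: Table 1 is the operative schedule, and allocation is hidden from participants when they complete the rating.

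The consequence is for interpretation. A positive PSQI result could be separated from unequal credibility only weakly, mainly through an end-of-treatment guess that may partly reflect perceived benefit. The treatment effect estimate is not altered. The change is worth making before participants are treated, but it is not a fault that undermines the primary analysis.

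**What to change.** Add a tick in Table 1 for the same 4-item questionnaire, in both arms, after an early session in Week 1. Have a blinded assessor collect it, and compare the arms. Keep the Week 0 rating and label it baseline expectancy. Revise the Assessment of Credibility section so that it names both time points and says what each rating is for. Leave the Week 4 blinding assessment in place.

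The cost is a few minutes for one short questionnaire at a visit that already takes place. If recruitment has not begun, no collected data are affected.
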